## Abstract

**Background/objectives:**

Around 11,500 artificial eyes are required yearly for new and existing patients. Artificial eyes have been manufactured and hand-painted at the National Artificial Eye Service (NAES) since 1948, in conjunction with approximately 30 local artificial eye services throughout the country. With the current scale of demand, services are under significant pressure. Manufacturing delays as well as necessary repainting to obtain adequate colour matching, may severely impact a patient’s rehabilitation pathway to a normal home, social and work life. However, advances in technology mean alternatives are now possible. The aim of this study is to establish the feasibility of conducting a large-scale study of the effectiveness and cost-effectiveness of digitally printed artificial eyes compared to hand-painted eyes.

**Methods:**

A cross-over, randomised feasibility study evaluating a digitally-printed artificial eye with a hand-painted eye, in patients aged ≥18 years with a current artificial eye. Participants will be identified in clinic, via ophthalmology clinic databases and two charity websites. Qualitative interviews will be conducted in the later phases of the study and focus on opinions on trial procedures, the different artificial eyes, delivery times, and patient satisfaction.

**Discussion:**

Findings will inform the feasibility, and design, of a larger fully powered randomised controlled trial. The long-term aim is to create a more life-like artificial eye in order to improve patients' initial rehabilitation pathway, long term quality of life, and service experience. This will allow the transition of research findings into benefit to patients locally in the short term and National Health Service wide in the medium to long term._

**ISRCTN registration:**

ISRCTN85921622 (prospectively registered on 17/06/2021)

## Introduction

The National Artificial Eye Service in England, UK has over 48,000 patients in its database alone and around 1,417 patients have surgery to remove their eye each year^1^. Replacement artificial eyes are made every 2-6 years for adults, with around 11,500 artificial eyes required yearly for new and existing patients. These eyes are manufactured by the National Artificial Eye Service (NAES) in conjunction with around 30 local artificial eye services. With such a level of demand, services are under increasing pressure which can result in delays in provision of artificial eyes.

Following an operation to remove a diseased eye, such as for eye cancer, a well fitted, life-like artificial eye can help rehabilitation. However, many patients suffer from anxiety and depression associated with their perceived disfigurement^2–4^, although the impact on Health-Related Quality of Life (HRQoL) is unknown.

The NAES has hand-painted artificial eyes since its integration into the National Health Service (NHS) in 1948. Local orbital prosthetists see patients in clinics, and use a non-standardised set of artificial eyes to colour match the appearance of the unaffected eye. A centralised site of laboratory technicians then manufacture the eye in six to ten weeks. However, achieving a good colour match is difficult and often requires multiple revisions.

This issue has been highlighted by Patient and Public Involvement (PPI) representatives as causing distress and delaying rehabilitation: many reported waiting up to 1 year for a good match. Family members or friends (hereafter called close contacts) are also impacted by the quality of artificial eyes as ill-matching eyes can cause distress. Digital photography for colour matching only the iris, and not the rest of the eye, have been described previously^5^.

These issues prompted the novel design and development of digitally-printed artificial eyes by Leeds Artificial Eye Service (LAES), Leeds, UK. Early work demonstrated that patients can receive a more life-like match, often within 2 weeks and requiring fewer multidisciplinary clinic visits.

Further research has to determine whether digitally printed eyes result in improvements in patients’ HRQoL and satisfaction. A large-scale randomised controlled trial (RCT) is needed to evaluate the effectiveness and cost-effectiveness of digitally-printed compared to hand-painted artificial eyes in order to inform clinical practice. First, we will undertake a feasibility RCT to see if it is possible to conduct a larger study.

## Study aims and objectives

The primary aim of this study is to determine the feasibility of conducting a RCT of the effectiveness and cost-effectiveness of digitally-printed artificial eyes compared to hand-painted eyes.

The specific objectives are to: -Determine the eligibility rate;-Determine patient recruitment rates;-Identify retention rates, data fidelity and missing data;-Identify a primary outcome measure(s) for a future trial (if feasibility established – by considering the amount of missing data, and any ceiling/floor effects seen within the measures);-Test study procedures and data collection tools and management;-Establish scalability of the current service.

The feasibility of the future trial will be assessed based on whether: -Patient recruitment and retention rates indicate recruitment for a full-scale RCT is plausible;-Outcome measures and fidelity evaluation data are successfully collected. Measures with over 10% missing data may be modified/replaced prior to the main trial;-Qualitative data confirms willingness of patients to be recruited, randomised and find research processes acceptable; and healthcare professionals’ opinions on the different artificial eyes, views on delivery times and patient satisfaction proves acceptable.

## Subjects and methods

### Study design

The study is a single centre, cross-over, randomised controlled, open feasibility study. Eligible patients who provide written informed consent will be randomised to: A:receive a digitally-printed artificial eye first (intervention), followed by a hand-painted artificial eye (control); orB:receive a hand-painted artificial eye first, followed by a digitally-printed artificial eye.

A flow diagram demonstrating participant pathway through the study is provided in Figure 1. Participants will be asked to attend five clinics approximately 2 weeks apart. Clinic 1- final eligibility, consent and baseline data; Clinic 2 – fitting of first eye; Clinic 3 – follow-up data on first eye; Clinic 4 - fitting of second eye; Clinic 5 – follow-up data on second eye and qualitative interviews. Between Clinics 3 and 4, participants can either continue to wear the first allocated eye, or revert to their original artificial eye. No concomitant care or interventions are prohibited (with the exception of participation in other artificial eye studies) and participants are allowed to keep their original artificial eye during the study.

All study documents including consent forms and data collection forms can be found as *Extended data*^6^.

### Setting

LAES at Leeds Teaching Hospitals NHS Trust will conduct participant identification, assess eligibility, consent participants and deliver the interventions.

Artificial eyes are classed by the Medicines and Healthcare products Regulatory Agency (MHRA) as “custom-made medical devices” intended for the sole use of a particular patient. Products manufactured in-house in a healthcare establishment that is conducting the study are not subject to the provisions of UK Medical Devices Regulations 2002, provided that the device is being manufactured and used on patients within the sole legal entity. There is no objective/intention to place the device on the market, and we manufacture the device inhouse for our own patients within Leeds Teaching Hospitals NHS Trust and therefore in the context of this study, does not constitute a medical devices trial requiring MHRA notification.

### Study population

#### Inclusion criteria

aged ≥ 18 years old;longstanding artificial eye user (≥12 months post-operation);requires a replacement artificial eye;able to complete the English language outcome measures (independently or with assistance).

#### Exclusion criteria

ongoing clinical concerns with respect to their artificial eye use (e.g. poor eye socket healing, extrusion, dehiscence);has bilateral artificial eyes;pregnant women or persons currently shielding (due to ongoing pandemic, to avoid unnecessary visits to clinic);currently participating in another study evaluating their artificial eye;unable or unwillingness to provide written informed consent.

#### Recruitment

Prospective participants will be identified via three main methods: in clinic, via database screening, or via notification placed on the Royal National Institute of Blind People and Blind Veterans UK websites.

Patients will be handed or posted a study invitation pack containing a Patient Invitation Letter, Participant Information Sheet, a Consent to Contact form, information pack for a close contact, and a pre-paid envelope. Patients will be asked to return the Consent to Contact form to York Trials Unit (YTU) if they wish to be contacted about the trial. Upon receipt of a patient’s Consent to Contact form, YTU will contact them to discuss any queries. The contact details of patients who are willing to be assessed for eligibility will be passed to LAES to arrange an appointment.

#### Eligibility and consent

Interested patients will be given an appointment to attend clinic for a final eligibility assessment.

Interested patients will be asked to approach a close contact (e.g. friend, family member, spouse), who might be willing to participate alongside the patient, in which case a specific information pack will be provided. Patients can take part without a close contact, but not vice versa.

If eligible and willing, written informed consent will be obtained from patients and, if applicable, their close contacts according to Good Clinical Practice guidelines.

#### Baseline assessment

Following consent procedures, baseline data will be collected according to the schedule in Table 1.

Eye history and assessment will include past medical history; past ocular and artificial eye history; current medications; and artificial eye socket examination (general socket health, fit and comfort of artificial eye, any current problems).

#### Randomisation

Following consent and baseline data collection (to ensure allocation concealment), an authorised team member at site will access a secure internet-based service hosted by the UKCRC-accredited YTU to obtain the order of the participant’s treatment allocation. Participants will be randomised on a 1:1 basis using block randomisation. Block sizes will not be disclosed, to ensure concealment. No stratification will be used.

### Level of masking

By the nature of the study treatments, masking of participants and clinic staff is not possible and procedure for un-masking is not necessary.

### Study treatments

All participants will have an eye socket impression taken for a fitted artificial eye. The artificial eye shape will be made by the LAES maxillofacial laboratory.

#### Digitally printed artificial eye (Intervention)

Digital photos of the unaffected eye will be printed onto specialised adhesive paper pressed onto the artificial eye.

#### Hand-painted artificial eye (Control)

Colour matching the unaffected eye will be done by the imaging department using a colour guide. The artificial eye shape and colour guide number are then sent to iProsthetics (Norwich, UK), to hand-paint and encapsulate with acrylic the artificial eye.

Each eye will be worn for at least two weeks. Attendance at clinics will be facilitated by participants having any travel expenses for additional protocol visits reimbursed. It is hoped this will increase adherence to the protocol in terms of clinic visits. Participants will be able to retain both new artificial eyes following study completion.

### Data collection

A summary of all data collection is presented in Table 1.

### Feasibility data

Data collected relating to recruitment will be: number of eligible patients, and the proportion of those that were screened: number approached for consent and not approached (and reason why); number approached who provide consent and do not provide consent (and reasons why). In addition, proportion of randomised participants withdrawing (with reasons) and lost to follow-up will be collected (and reason why, where possible).

### Staff-collected data and preference questionnaire

Staff will collect data at baseline, Clinic 3 and Clinic 5 which will include information on eye socket health and adverse events (AEs). Data will also be collected at each clinic on tasks undertaken (including manufacturing steps both eyes) and time taken.

Following completion of the study by all participants, the healthcare professionals will also be asked to view eye-band images comparing both eyes, stating which they prefer.

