### Close contact data

Close contacts will be asked to complete a study-specific satisfaction questionnaire after their friend/relative has worn each eye (Clinics 3 and 5) and asked to compare photographs of both eyes stating a preference (Clinic 5).

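### The reason given for not masking does not reach the staff's image preference, which could be rated from coded images in random position

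*Protocol article*

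**What the plan says.** The Level of masking section of the protocol article is one sentence. It gives as its reason "By the nature of the study treatments" and concludes that "masking of participants and clinic staff is not possible and procedure for un-masking is not necessary". Study design agrees: "The study is a single centre, cross-over, randomised controlled, open feasibility study".

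The section on staff-collected data adds a task that starts only once every participant has completed the study: "the healthcare professionals will also be asked to view eye-band images comparing both eyes, stating which they prefer". Table 1 lists it as a data item. The article does not say whether the images are labelled, coded or randomly placed, and it does not define who the professionals are.

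Two other places bear on the raters. The Introduction credits the "novel design and development of digitally-printed artificial eyes by Leeds Artificial Eye Service". Setting has the same service identify, assess and consent participants and deliver the interventions.

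Under Analyses, categorical data are to be given as counts and percentages, with no hypothesis testing for effectiveness.

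**The concern.** A preference between two photographs is easily influenced by knowing which product is which. The risk is greater when the rater has a professional stake in one of them. The long-term aim in the Abstract and Conclusion is a more life-like eye, and a side-by-side image choice addresses appearance directly. If the choice is made with knowledge of the eye type, the resulting percentage mixes perceived quality with expectation, and nothing in the data would separate the two.

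The absence of a significance test does not remove this. A reported percentage is biased or not regardless of whether a p-value stands beside it. The objectives also include testing study procedures and data collection tools. Whether staff can rate images without knowing the type is a question this study could answer for a later trial. A statement that masking is impossible closes off that question without considering it.

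**Working it through.** No figure in the protocol depends on this point, so the check is mainly a comparison of the relevant sections.

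**1. Does the stated reason cover each assessment?**

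- *Wearing an eye and reporting on it (participants, Clinics 3 and 5).* The participant lives with the eye and sees how it was made. The reason applies.
- *Making and fitting an eye and checking the socket (clinic staff).* One route prints a photograph of the unaffected eye. The other uses a colour guide and an external firm that paints the eye. Staff handle the product, so the reason applies.
- *Choosing between two eye-band images (healthcare professionals, after all participants finish).* No eye is being made, fitted or worn for the study at that point. The material is a pair of image files, which can be stripped of labels and shuffled. The reason does not apply.

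The masking statement therefore gives one general reason, while the same article schedules a staff assessment that the reason does not reach.

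**2. Who probably rates?** The study has one centre, Leeds Artificial Eye Service delivers the interventions there, and the Introduction says that service developed the digital eye. It is likely, though not stated, that the raters are largely its staff. The approximately 5 staff from named teams, under Qualitative data collection, are invited to interviews and are not identified as image raters.

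**3. What could expectation do to the percentage?** The document gives nothing from which to size the bias, so this is an illustration only. Assumptions: 30 image pairs, one rating per pair, ratings independent, no true preference, and a share *b* of ratings going to the digital eye because its type is known. The 30 comes from the sample size section (35 recruited, 15% attrition: 35 × 0.85 = 29.75, about 30).

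Probability of choosing digital: *p* = *b* + (1 − *b*) × 0.5. Expected digital choices: 30 × *p*. The last column is the binomial probability of 21 or more out of 30 (70%).

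| *b* (assumed) | *p* | Expected of 30 | P(≥ 21 of 30) |
|---|---|---|---|
| 0 | 0.50 | 15.0 | 0.021 |
| 0.1 | 0.55 | 16.5 | 0.069 |
| 0.2 | 0.60 | 18.0 | 0.176 |
| 0.3 | 0.65 | 19.5 | 0.358 |
| 0.4 | 0.70 | 21.0 | 0.589 |

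The table shows the direction and mechanism. It does not estimate what will happen in this study.

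**The case against.** The strongest reply is that the article is silent on how the images are shown. It does not say they are labelled. Layout and labelling belong in the rating form or the full protocol, both of which the article says are posted as extended data, and an article may leave such detail to them. This stands in part. A reader might infer that the plan schedules a labelled, unmasked comparison, and the text does not establish that. But the article is not silent on masking as such: it calls the study open and says clinic staff cannot be masked. If the fuller documents do code the images, the masking sentence is misleading as it stands and still needs limiting.

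Second, the raters are undefined, so a reader who takes them to be the developers goes beyond the text. It is a reasonable inference and no more.

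Third, staff who made or fitted an eye may recognise it, so coding may not fully mask them. This stands, and it is why a guess item is needed. The same reasoning limits the point to staff. A reader might want the participants' and close contacts' image choices masked too, but they have seen each eye worn for at least two weeks, so unlabelled images would hide little from them.

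Fourth, a reader might fault percentages pooled over raters and participants. The article gives only a general rule for categorical data, specifies no pooling or interval for this item, and defers the analysis to a statistical analysis plan. No criticism of the analysis follows.

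Finally, the feasibility criteria include professionals' opinions on the eyes, which a plain preference may serve, and do not name the image item. That lowers the weight of the point but does not justify leaving an avoidable bias in place.

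**Conclusion.** The point holds at low severity. The stated reason for not masking covers wearing, fitting and self-report. It does not cover a staff choice between photographs made after the last participant has finished. As written, the staff preference percentage is open to expectation bias that a simple procedure would reduce.

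The size of the bias cannot be derived from the document. The conclusion rests on two readings: that the general masking statement is meant to apply to clinic staff in this task as well, and that the raters come largely from the developing service. The first follows from the absence of any exception. The second is probable but not stated.

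Two stronger conclusions are not supported. One is that the preference would carry no credible information: it would still record professional opinion, though possibly coloured by knowledge of the eye type. The other is that masking would cost nothing: the document gives no cost, and some preparation is needed. The item is secondary and descriptive, and it is not a named basis for deciding whether a full trial is feasible.

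**What to change.** In Level of masking, limit the statement to wearing, fitting and self-reported outcomes.

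In the staff-collected data section, state that:

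- healthcare professionals rate coded, unlabelled, identically framed images;
- the trials unit randomises left/right position and the order of participants;
- the trials unit holds the key until the ratings are locked;
- each rater also guesses which eye is digital in each pair, as a check on masking.

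The same section should say who the raters are. If the full protocol or forms already specify any of this, a sentence saying so is enough.

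The cost is minor: preparing the image files and a randomised list, with no extra visits and no change to treatment. The article reports that data collection is ongoing and the staff ratings come after all participants finish, so the change may still be possible. The downside is that masking may be incomplete among staff who made or fitted the eyes. The guess item would show how far that happened and let the result be read accordingly.

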### Participant self-reported data

At baseline, Clinic 3 and Clinic 5 the following participant self-reported data will be collected: Short Form 36 (SF-36): a generic HRQoL measure^7^.EQ-5D-5L (EuroQol-5 dimensions-5 levels): a generic HRQoL measure^8^.Vision Quality of Life Index (VisQol): assesses impact of vision loss^9^.Connor-Davidson Resilience Scale-10 (CD-RISC-10): provides a measure of resilience^10^.Derriford Appearance Scale short form (DAS24): assesses distress and difficulties in living with disfigurement and problems of appearance^11^.Participant satisfaction: a brief study-specific questionnaire to assess participant satisfaction using a 0–10 scale. Eye-band image selection comparing both eyes will also be used.Resource use: a study-specific questionnaire on hospital attendances, admissions, and primary care visits (e.g. GP, nurse), in relation to their artificial eye.

### Qualitative data collection

Qualitative interviews will be done in the later phases of the study and focus on opinions on trial procedures, the different artificial eyes, delivery times, and patient satisfaction. The study consent form will also contain statements in relation to consent to interview for this qualitative aspect of the study. Re-confirmation of consent will be taken verbally prior to commencement of the interview. A subset of participants (approximately N=15), and their close contacts (approximately N=15) will be interviewed after both artificial eyes have been trialled. Interviews, lasting ~45 minutes, can be done face-to-face at a location of the person’s preference, over the phone, or via video-call and will be audio-recorded. Where possible, individual interviews will be conducted to allow each member of the dyad to freely express their feelings. Data collection will continue until saturation is achieved^12^.

Approximately 5 members of the manufacture, ophthalmology, maxillofacial, and prosthetists teams will be invited to take part in a semi-structured interview lasting ~20 minutes. Following consent, interviews will take place face-to-face, over the phone or via videocall.

### Close contact data

Close contacts will be asked to complete a study-specific satisfaction questionnaire after their friend/relative has worn each eye (Clinics 3 and 5) and asked to compare photographs of both eyes stating a preference (Clinic 5).

